## Abstract

**Background:**

Postoperative upper gastrointestinal fistula (PUGIF) is a devastating complication, leading to high mortality (reaching up to 80%), increased length of hospital stay, reduced health-related quality of life and increased health costs. Nutritional support is a key component of therapy in such cases, which is related to the high prevalence of malnutrition. In the prophylactic setting, enteral nutrition (EN) is associated with a shorter hospital stay, a lower incidence of severe infectious complications, lower severity of complications and decreased cost compared to total parenteral nutrition (TPN) following major upper gastrointestinal (GI) surgery. There is little evidence available for the curative setting after fistula occurrence. We hypothesize that EN increases the 30-day fistula closure rate in PUGIF, allowing better health-related quality of life without increasing the morbidity or mortality.

**Methods/design:**

The NUTRILEAK trial is a multicenter, randomized, parallel-group, open-label phase III trial to assess the efficacy of EN (the experimental group) compared with TPN (the control group) in patients with PUGIF. The primary objective of the study is to compare EN versus TPN in the treatment of PUGIF (after esophagogastric resection including bariatric surgery, duodenojejunal resection or pancreatic resection with digestive tract violation) in terms of the 30-day fistula closure rate. Secondary objectives are to evaluate the 6-month postrandomization fistula closure rate, time of first fistula closure (in days), the medical- and surgical treatment-related complication rate at 6 months after randomization, the fistula-related complication rate at 6 months after randomization, the type and severity of early (30 days after randomization) and late fistula-related complications (over 30 days after randomization), 30-day and 6-month postrandomization mortality rate, nutritional status at day 30, day 60, day 90 and day 180 postrandomization, the mean length of hospital stay, the patient’s health-related quality of life (by self-assessment questionnaire), oral feeding time and direct costs of treatment. A total of 321 patients will be enrolled.

**Discussion:**

The two nutritional supports are already used in daily practice, but most surgeons are reluctant to use the enteral route in case of PUGIF. This study will be the first randomized trial testing the role of EN versus TPN in PUGIF.

**Trial registration:**

ClinicalTrials.gov: NCT03742752. Registered on 14 November 2018.

## Background

The incidence of clinically significant postoperative upper gastrointestinal fistula (PUGIF) surgery is approximately 4%–20%, and the associated mortality can be as high as 80% [1]. Various clinical presentations are described that can endanger the patient’s life. It is important to start explorations without delay when the diagnosis of PUGIF is made as delayed management could lead to a devastating prognosis. Optimal communication between the teams is mandatory for successful treatment. When the clinical presentation is an important and acute sepsis the treatment should be surgical, but when the clinical presentation is less symptomatic or late the treatment should be more conservative with a watch-and-wait or endoscopic management [2, 3]. The diagnosis should be made with the help of computed tomography (CT) scans with oral contrast and low-insufflation early endoscopy. The principles of treatment include transfer to the intensive care unit, optimal perfusion, intensive physiotherapy, antifungal and antibiotic treatment, and eventually drainage and collection or fistula closure (when possible) in the absence of ischemia [2].

Some promising endoscopic techniques in the treatment of PUGIF have been reported (such as over-the-scope (OVESCO)-clip®), mainly in bariatric surgery and often in case reports [4]. The results give information on feasibility but are too weak to give information on efficiency. Large defects cannot be treated with hemostatic clips [2, 4, 5]. The fistula output can be reduced by somatostatin analogs [3, 6].

Several prognostic factors of PUGIF have been identified [7], such as high output, high concentration of toxic bile acids and active digestive enzymes, a fistula tract longer than 2 cm, elevated postoperative blood glycemia [8] and malnutrition with serum albumin <30 g/l [3].

Nutritional support is a key component of PUGIF management, related to the high prevalence of malnutrition and nil-per-mouth requirements for fistula treatment [9, 10]. Therefore, despite fasting, nutritional support is mandatory, and both enteral nutrition (EN) downstream of the site of leakage (via a feeding jejunostomy or a nasojejunal feeding tube placed radiologically or endoscopically) [11] and parenteral nutrition are possible and currently used. However, the role of EN in maintaining the small intestinal structure and function and in improving postoperative outcomes is well established. Enteral nutrients maintain the structural function that are compromised by fasting and parenteral nutrition [12, 13].

In the prophylactic setting (i.e., in a population without fistula but at the risk of developing one) a published systematic literature review [1] based on seven randomized trials showed that EN is associated with shorter hospital stay, lower incidence of severe infectious complications [14], lower severity of complications and decreased costs compared to total parenteral nutrition (TPN) following major upper gastrointestinal (GI) surgery [1, 15].

In the curative setting (after fistula occurrence) there is evidence available. Only one randomized clinical trial has suggested the superiority of EN over TPN after pancreatic surgery, with an increase in the 30-day fistula closure rate from 37% in the TPN group to 60% in the EN group [16]. This trial only included pancreatic fistula and did not include all PUGIFs that can also occur after esophagogastric resection, including bariatric surgery, duodenojejunal resection or pancreatic resection with digestive tract violation, although the concept of enteral nutritional support is highly relevant in all these situations. Even if EN seems to be promising, the potential risk of increasing the leakage output related to a reflux of nutritional liquid and/or to activate digestive enzymes, consequently reducing the probability of fistula closure rate or increasing the delay of fistula closure, may explain why surgeons are usually reluctant to provide EN [4]. A few, small randomized studies suggested the feasibility of EN in 47 patients with upper GI fistula [17] for the treatment of esophagojejunal fistula after total gastrectomy in gastric cancer patients [18] and after PUGIF following sleeve gastrectomy [19, 20], but to date no randomized study has been designed to test the superiority of EN versus TPN in PUGIF.

Our study aim is thus to demonstrate the superiority of EN over TPN in accelerating fistula healing after upper GI surgery.

## Methods/design

### Protocol overview

The NUTRILEAK trial is a multicenter, randomized, parallel-group, open-label, phase III study to assess the efficacy of EN compared to TPN in patients with PUGIF. After informed consent, patients will be randomized in a 2:1 ratio to the EN treatment arm and the TPN comparator arm. Patients will be randomized to receive EN through jejunostomy or nasojejunal tube, or to receive TPN through central venous access, a peripherally inserted central catheter line, totally implantable venous access or any other approved TPN device.

Any other surgical or endoscopic procedures aiming at directly closing the defect will not be allowed (including surgical closure and endoscopic clip, prosthesis or glue) throughout the whole study period. These measures have not been scientifically demonstrated to be efficient in this situation at this time and could be a confounding factor regarding our primary objective.

By contrast, surgical, radiological or endoscopic fistula drainage will be allowed throughout the whole study period. Any interruption of more than 24 h in the treatment determined by randomization (EN or TPN) will be reported, with the cause, duration and solutions given (i.e., the treatment provided or a switch to TPN in the EN group). During hospitalization, patients will be evaluated daily until fistula closure, with any fistula- or protocol treatment-related complication viewed through physical examination and, if required, through routine laboratory tests and/or imaging according to the usual practice of each center.

The present study protocol was written in compliance with the Standard Protocol Items: Recommendations for Interventional Trials (SPIRIT) 2013 [21]. A completed SPIRIT checklist is available as Additional file 1, and the schedule of this study is presented in Fig. 1.

**Fig. 1 Fig1:**
[figure not shown]
Schedule of the trial interventions and assessments. *Enteral nutrition (EN) or total parenteral nutrition (TPN) will be continued until the oral intake reaches at least 60% of daily requirements. **Computed tomography (CT) scan with contrast injection for patient who do not show any output of fluid during 48 h in wound or drainage. EQ5D EuroQol five dimensions, SF-36 36-item Short Form

The study flowchart is shown in Fig. 2.

**Fig. 2 Fig2:**
[figure not shown]
Flowchart of the trial. D day, EN enteral nutrition, GI gastrointestinal, TPN total parenteral nutrition, V visit

### Objectives

The primary objective is to demonstrate the superiority of EN over TPN in the treatment of PUGIF after esophagogastric resection including bariatric surgery, duodenojejunal resection or pancreatic resection with digestive tract violation in terms of the 30-day fistula closure rate.

Secondary objectives are the assessment of: 1) 6-month postrandomization fistula closure rate; 2) time of first fistula closure (in days); 3) medical and surgical treatment-related complication rate (EN or TPN) at 6 months after randomization; 4) fistula-related complication rate at 6 months after randomization; 5) type and severity of early (30 days after randomization) and late (over 30 days after randomization) fistula-related complications; 6) 30-day and 6-month postrandomization mortality; 7) nutritional status at day 30, day 60, day 90 and day 180 postrandomization; 8) mean length of hospital stay; 9) patient health-related quality of life (by self-assessment questionnaire); 10) time for oral feeding; and 11) direct costs of treatment.

### Inclusion criteria

All patients diagnosed with a postoperative digestive fistula in the recruiting centers will be screened for eligibility to participate in the study. Inclusion criteria are patients who: 1) are older than 18 years of age; 2) signed the written informed consent form (Additional file 2); 3) underwent upper GI surgery for benign or malignant disease (i.e., esophagogastric resection including bariatric surgery, duodenojejunal resection or pancreatic resection with digestive tract violation); 4) have had the diagnosis of an active postoperative digestive fistula untreated or persisting after failure of a dedicated surgical or endoscopic procedure to close the fistula (the fistula should have been diagnosed less than 72 h before randomization and confirmed by at least two criteria among the following: clinical symptoms, CT scan/ultrasonic imaging/endoscopic diagnosis, biologic/bacteriology diagnosis on fluid output, intraoperative diagnosis at time of reoperation); 5) have the indication of nil-per-mouth or just clear liquids for comfort; 6) require an artificial nutritional support; 7) have an American Society of Anesthesiologists (ASA) score of 1, 2 or 3; 8) have a life expectancy longer than 6 months; 9) have no history of allergy or product intolerance to the nutritional product used in the study; 10) have ongoing healthcare insurance; and 11) are able to understand the information letter.

### Exclusion criteria

Patients with any of the following criteria will not be included in the study: 1) scheduled surgical or endoscopic treatment with the aim of closing the fistula (suture, prosthesis, clip or glue); in case of treatment failure, patients are eligible to participate to the study; endoscopic or surgical drainage are not exclusion criteria (meaning that drainage is authorized only before randomization); 2) patient diagnosed with an isolated pancreatic fistula (without digestive content) after a pancreatic resection without digestive tract violation; 3) history of current severe uncontrolled cardiovascular, pulmonary, renal or liver failure; 4) presence of a severe and evolutive life-threatening pathology; 5) uncontrolled sepsis/situation related to the fistula (including, but not limited to, abscess, bleeding, fistula with the trachea or the aorta); 6) requirement of a nutritional support combining both the enteral and parenteral routes together; 7) peritoneal carcinomatosis or distant metastasis; 8) pregnant and/or lactating women; 9) freedom privacy; and 10) patient currently participating or having participated in another interventional clinical trial related to nutritional support or fistula management during 30 days prior to the beginning of the study (note that participation in a prior clinical trial not related to nutritional support or fistula management does not exclude the patient from participation).

### End points

The primary end point is the fistula closure rate at 30 days after randomization. Fistula closure will be defined as no output fluid for 48 h in the wound or drainage and absence of any fluid collection on imaging (CT scan with contrast injection). The secondary end points are: 1) 6-month fistula closure rate; 2) time of first fistula closure, defined as time in days from randomization to first fistula closure within 6 months after randomization; 3) medical and surgical treatment-related complication rate at 6 months, including complications related to the nutritional support such as tube -related complications (dislodgment, infection, occlusion), venous catheter -related complications (thrombosis, infection), or any other nutritional route-related complications; 4) fistula-related complication rate at 6 months; 5) type and severity of early (before 30 days after randomization) and late (over 30 days after randomization) complications according to the Dindo–Clavien classification [22]; 6) mortality within 30 days and within 6 months after randomization; 7) nutritional status will be evaluated at day 30, day 60, day 90 and day 180 postrandomization based on weight, serum albumin and prealbumin concentration, C-reactive protein and grip test (muscular strength); 8) length of hospital stay in a health care structure (including home hospitalization) based on the cumulative number of days of hospitalization during the whole study period (from randomization until the end of the study); 9) patient health-related quality of life score based on the 36-item Short Form and EuroQoL five-dimensions questionnaires at inclusion and at days 30, 60, 90 and 180; 10) time from randomization to the oral diet covering at least 60% of the patient’s daily requirement ; 11) direct economic costs of therapy from a societal perspective, including the costs of hospitalization (inpatient and home settings), nutritional products, and early and late complications occurring during follow-up.

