### Randomization

Patients will be randomized at inclusion during hospitalization after verification of their suitability for inclusion. Patients will be randomized using the Clinsight system (ENNOV). Randomizing two cases for one control has been chosen based on the positive results of the study by Klek et al. exhibiting a higher 30-day fistula closure rate in the EN group for patients with pancreatic fistula, which has a similar context [16]. In addition, European guidelines are in favor of EN for patients needing artificial nutrition with a grade A level of evidence (without the context of PUGIF where nothing has been demonstrated to date). A dynamic randomization procedure by minimization will be performed to achieve a balance between the following prognostic factors: the type of fistula (high- versus low-output, where a high-output fistula is defined as effluent greater than 200 ml/24 h), malignant/nonmalignant disease, and somatostatin analog use. The variable of treatment center will also be considered in the minimization procedure. Taking into account the fistula outflow, stratification on the surgical procedure/organ will not be included in the minimization procedure since the two are strongly linked.

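### Entry requires neither wound or drain output nor a fluid collection, and closure is defined only by their absence, so a patient could already meet the closure definition at randomisation

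*Protocol article*

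**What the plan says.** **End point.** The End points section of the protocol article states: "The primary end point is the fistula closure rate at 30 days after randomization". It continues: "Fistula closure will be defined as no output fluid for 48 h in the wound or drainage and absence of any fluid collection" on imaging, the imaging being CT with contrast injection. The definition does not refer to the patient's state at randomisation. It also does not ask whether the leak or defect itself is still visible. Secondary end points 1 (closure at 6 months) and 2 (time to first closure) use the same notion of closure.

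**Entry.** Inclusion criterion 4 asks that patients "have had the diagnosis of an active postoperative digestive fistula untreated or persisting after failure of a dedicated surgical or endoscopic procedure" to close it. The diagnosis must be less than 72 h old at randomisation and rest on at least two of: "clinical symptoms, CT scan/ultrasonic imaging/endoscopic diagnosis, biologic/bacteriology diagnosis on fluid output, intraoperative diagnosis at time of reoperation". The word *active* is not defined in terms of output or collection.

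**Related text.** Under Exclusion criteria, "endoscopic or surgical drainage are not exclusion criteria", and an abscess excludes a patient only as part of an uncontrolled situation. Under Randomization, "a high-output fistula is defined as effluent greater than 200 ml/24 h", and no lower limit is given for the low-output class. Under Data collection and follow-up, patients without output for 48 h have a CT with injected and ingested contrast. Under Treatment methods, allocated nutrition may start up to 72 h after randomisation.

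**The concern.** The entry criteria establish that a fistula exists. The end point establishes that two of its possible signs are absent. Nothing in the text ties the second to the first, so a patient who had neither sign at entry could be counted as healed although nothing has changed.

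The primary end point is meant to show healing that the feeding route can influence. A patient who satisfies it from the start tells us nothing about that route. Such patients raise the closure rate in both arms and dilute the difference. In the time-to-first-closure analysis they would appear as closures at about day 0 to 2. That may be before any allocated nutrition has been given, since the 48 h dry period is shorter than the 72 h allowed for starting it. The intention-to-treat set keeps all of them.

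**Working it through.** **1. Can the text admit such a patient?** Four confirmatory findings give six pairs. Three of them involve the laboratory finding on fluid output. The other three do not:
- symptoms with imaging or endoscopy
- symptoms with intraoperative diagnosis
- imaging or endoscopy with intraoperative diagnosis

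No pair requires a collection. A patient who enters on one of these three pairs, with no drain, a closed wound and no collection, meets both halves of the closure definition once 48 h have passed. In the minimisation this patient falls into the low-output class, so that factor does not single the patient out.

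**2. The plan's own sample size.** Inputs from Statistical evaluation and sample size: 35% closure with total parenteral nutrition (TPN), 55% with enteral nutrition (EN), two-sided 5%, 90% power, 2:1 allocation, 10% mortality at 30 days.

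With pooled variance and no continuity correction, the mean rate is (0.35 + 2 × 0.55)/3 = 0.4833, and

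n(TPN) = [1.960 × √(1.5 × 0.4833 × 0.5167) + 1.282 × √(0.35 × 0.65 + 0.55 × 0.45/2)]² / 0.20² = (1.1996 + 0.7595)² / 0.04 = 95.95, so 96.

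That gives 96 TPN and 192 EN. Dividing by 0.90 gives 96/0.90 = 106.7, so 107 TPN, hence 214 EN and 321 in total. The stated figure is reproduced exactly.

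**3. Dilution.** Let f be the share that counts as closed in both arms. This is an assumption, since the documents give no value. Let 35% and 55% apply to the remaining patients. The rate in each arm is then f + (1 − f) × planned rate, and the difference is 0.20 × (1 − f).

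Power = Φ[(difference − 1.960 × SE₀)/SE₁], with 96 and 192 evaluable patients, SE₀ from the pooled rate and SE₁ from the separate rates:

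| f | TPN | EN | Difference (points) | Φ argument | Power | N for 90% power |
|---|---|---|---|---|---|---|
| 0 | 35% | 55% | 20 | (0.20 − 1.960 × 0.06247)/0.06049 = 1.282 | 90.0% | 321 |
| 5% | 38.25% | 57.25% | 19 | (0.19 − 1.960 × 0.06249)/0.06112 = 1.105 | 86.5% | 360 |
| 10% | 41.5% | 59.5% | 18 | (0.18 − 1.960 × 0.06235)/0.06151 = 0.940 | 82.6% | 402 |
| 20% | 48% | 64% | 16 | (0.16 − 1.960 × 0.06155)/0.06164 = 0.638 | 73.8% | 501 |

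The last column repeats step 2 with the diluted rates, including the 10% inflation.

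**4. Type I error.** If the feeding route has no effect, both arms have the same rate f + (1 − f)p. The null hypothesis is preserved and false-positive risk does not rise.

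**The case against.** The strongest reply is that such patients may hardly exist. Criterion 4 asks for an *active* fistula, and the design uses effluent as its working measure by minimising on it. Contained leaked fluid is ordinarily a collection, and any collection defeats closure. Drainage before randomisation does not help the concern much either: a drain gives a route by which an active leak shows output. Patients with controlled collections remain eligible and fail the definition at entry. This stands as far as frequency goes. A reader might infer that some patients do meet the definition at entry, but the documents support only that they could.

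A reader might also infer that these patients are certain to count as 30-day closures whichever arm they are in. The documents do not support that. The end point is closure at 30 days, and a patient dry at entry can develop output or a collection by then. The Background itself names increased leakage output as a feared effect of EN.

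The planned 35% and 55% are expected rates for the trial groups, based on a trial in pancreatic fistula. They may already include such patients, in which case the plan has absorbed part or all of the loss.

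Finally, this is a condensed article whose schedule figure is not shown, so a baseline CT or output check cannot be ruled out. But a baseline check would not alter the closure definition, which is given in the text and makes no reference to baseline. That part of the objection does not remove the point.

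**Conclusion.** The point holds as a mismatch between two rules that the protocol does state. As written, the closure definition can classify an unchanged leak as closed, in the primary end point and in time to first closure. That is more than a detail left to another document.

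The size is unknown and probably small. The calculated power of about 87%, 83% and 74% depends on f = 5%, 10% and 20%, and none of these values comes from the documents. The figures are best read as an upper bound on the loss for each f: they allow EN no benefit in these patients and assume that none of them is already reflected in 35% and 55%. That reading also needs these patients to do no worse under EN than under TPN. The harm is dilution and lost power, with no inflation of type I error. If no such patients are enrolled, 321 patients at 90% power stands.

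**What to change.** 1. Record at randomisation whether wound or drain output is present and whether a fluid collection is present.
2. In End points, keep the present definition and add that closure counts only when a sign present at randomisation has resolved.
3. For patients with neither sign at randomisation, require no contrast leak on the CT with ingested contrast. Data collection and follow-up already plans this examination for patients dry for 48 h, so no repeat endoscopy or reoperation is needed.
4. Apply the same rule to the 6-month closure rate and to time to first closure.
5. Add a sensitivity analysis of the primary end point without patients who met the closure definition at randomisation. Membership is fixed by baseline data, so leaving them out does not depend on anything that happens after allocation.

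The cost is two baseline fields, a short addition to the end-point definition and one further analysis. Closure rates may come out slightly lower.
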